### Outcomes of efficacy

Outcomes of pain, pain-related suffering and disability, depression and anxiety, functional status, motor abilities, and suicidal ideation are collected at several time points (Figure 1).

#### Primary endpoint

Instead of using the historically accepted criterion of 50% analgesia (using the VAS), we instead chose a 40% effect on the PDI as our primary endpoint. The PDI measures disability in physical and psychosocial categories spanning across domains such as family, sexual, social, recreational, self-care, occupational and life-support domains [25]. Its strong relationship with quality of life outcomes makes it equivalent and potentially superior to existing functional-status questionnaires used in pain research, such as the VAS [26].

#### Secondary endpoints

Secondary endpoints include: 1) 40% improvement in PDI in 50% of patients at 2-year follow up; 2) affirmative response to the prospect of receiving the treatment again if the same outcome were to be achieved; and 3) 50% reduction in VAS at 2-year follow up.

Other outcomes include neuropsychological pain, and cognitive and psychiatric assessments (Figure 1, Table 1) as follows:

•The McGill Pain Questionnaire consists of descriptors of pain, including sensory, affective, evaluative and miscellaneous categories [27]

•The Beck Depression and Anxiety Inventories are self-report measures to document the level of depression [28] and anxiety and have been used in DBS studies of chronic neuropathic pain [5]

•Tests of manual dexterity: the box and block test specifically measures the grasp and release function of the paretic hand.

•EuroQOL (EQ-5D VAS) is a measure of health-related quality of life that has been employed in previous DBS studies in neuropathic pain [29]

•C-SSRS [30] provides valid, sensitive and specific assessment of suicidal ideation and behavior

•MADRS is a valid, acceptable, reliable and sensitive patient-reported outcome assessing severity of depression [31]

•Neuropsychological tests of cognitive function will include the California Verbal Learning Test, the Wechsler memory Scale, the Delis-Kaplan Executive Function System and the Wisconsin Card Sorting Test

In functional neuroimaging, fMRI and MEG are utilized to help define affective-cognitive networks associated with allodynia and anticipation of pain in chronic TPS, and their potential modulation with DBS of the VS/ALIC; fMRI has been performed safely in patients with DBS implants in our previous studies [32]. Our group has demonstrated that DBS delivered specifically to the VS/ALIC is associated with cortical-subcortical fMRI activation that represents affective networks in the brain [32]. MEG use with implanted DBS has also been shown to be safe and feasible [33,34]. We chose to utilize both fMRI and MEG to reveal substrates of affective dimension of pain because their unique strengths are complementary. Whereas fMRI is associated with superior spatial resolution, MEG possesses very high temporal resolution [35].

Both MEG and fMRI are exploratory in this study. With fMRI, one of our goals is to evaluate resting state fMRI, comparing networks when DBS is turned on versus when it is turned off. Patients will undergo resting-state fMRI at pre-operative baseline, during the randomized blinded phase and during follow up. Thus, by comparing the DBS-on and DBS-off conditions, we will be able to assess the effects of active versus sham DBS without confounds related to placebo or study-related effects. The next goal is to correlate changes in the neural networks related to the placebo effect; we intend to do so by comparing effects of DBS-off stimulation between active, sham and pre-operative baseline phases. With MEG, we aim to harness its high temporal resolution to assess possible effects of DBS on pain anticipation. The primary hypothesis is that DBS will have a significant effect upon the affective sphere of chronic pain. Pain anticipation is one of the conditions leading to pain habituation and chronic pain. Thus, we theorize that improvements in the affective sphere will also be correlated to how cortical networks in patients with TPS modulate in pain anticipation. In order to test this concept, we have created a visual paradigm of pain anticipation that consists of a simple, three-second countdown. The type of visual paradigm encodes whether or not a painful stimulus would follow the countdown. One of the limitations related to this paradigm is that we do not have a full characterization of how healthy individuals respond to pain anticipation in this task. This can limit our understanding of how processing of pain anticipation is abnormal in individuals with TPS, and could as well limit the interpretation of effects of active DBS. In order to address these limitations, we are also evaluating a cohort of 10 healthy subjects to allow comparisons.

### Statistical and data analysis plan

#### Safety and feasibility

The goal of this study is to evaluate the safety and feasibility of delivering DBS to the VS/ALIC in patients with TPS in a double-blinded, randomized, sham-controlled, crossover clinical trial. A Data Safety and Monitoring Board (DSMB) has been established as an advisory group to evaluate adverse events and judge overall integrity and conduct of the study. DSMB review at the outset, half-way through the enrollment process and at the end, will record numbers of participants enrolled, participants lost to follow up, deviations from protocol, threats to blinding and adverse events, following which, decisions about continuation or recommendations for changing or ending the study could be made.

If DBS is acutely and significantly effective in patients who are randomized to receive DBS of the VS/ALIC first, then there is a chance that patients may notice substantial worsening of the pain (assuming that the intervention is effective) and the validity of the experimental blinding may be compromised. In this case, to investigate the effect on blinding, we will record the patient’s and the blinded investigator’s subjective perception (to the best of their ability to guess) of whether active DBS or sham was being delivered during the blinded phase. If the relapse in pain is considered to be threatening or if there is suicidal ideation, then stimulation will be re-initiated and/or patient will be allowed to escape randomization [20,36]. On the other hand, if patients receive sham stimulation first, a relapse in pain will be managed with medical management at that time, because we do not anticipate much change in their baseline pain.

#### Sample size estimation and efficacy

Since the study is designed as a randomized, sham-controlled, double-blinded study, we will also be able to evaluate whether any potential trend indicates efficacy, which would help compute effect sizes and variance in DBS versus sham phases to estimate sample sizes for adequate power in future. Our within-subject, crossover design would also yield the magnitude of placebo effect related to the surgical process itself that is an important practical issue to consider in effect-size estimates for the future.

This study was initially planned to involve a total of 34 patients. The sample size was estimated based on changes in PDI in patients with central pain syndrome in an earlier study [37]. It was determined that to detect an effect size of 0.5 (equivalent to a 7-point decrease in PDI), a total of 34 patients would need to have been included for statistical power of 80% on a two-sided test with a type I error probability of 0.05. The Food and Drug Administration of the United States has, however, determined in its review that the study should initially enroll 10 patients as part of a phase I, safety study.

Due to the small sample size of the proposed pilot phase I trial, procedures for corrections for multiple comparisons cannot be instated; the scope of the subsequent phase II trial would be better suited to include such procedures. By examining only a priori hypotheses, we aim to mitigate the probability of making type I errors. Therefore, we will compare the differences in the primary and secondary outcomes in the third month of DBS with those in the third month of sham stimulation using the paired *t*-test at α = 0.05. Despite the sample size limitation, we expect the study to be informative in estimating the magnitude of the placebo effect after DBS for pain, as well as variances in outcome that to date are unknown. These will be valuable in designing subsequent phase II and III studies.

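### A sample of 10 does not rule out multiplicity control: testing PDI first or alone at 0.05 costs it nothing, yet the plan tests secondary outcomes unadjusted at 0.05 (minor)

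*Protocol article*

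**What the plan says.** All the relevant statements are in the protocol article, in the last paragraphs of Sample size estimation and efficacy.

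- On correction: owing to the small sample, "procedures for corrections for multiple comparisons cannot be instated". The article adds that such procedures belong in the later phase II trial.
- On the substitute: "By examining only a priori hypotheses, we aim to mitigate the probability of making type I errors".
- On the analysis, introduced as following from this: the investigators will "compare the differences in the primary and secondary outcomes in the third month of DBS" with the matching month of "sham stimulation using the paired *t*-test at α = 0.05".

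No testing order, alpha split or descriptive label for the secondary p-values is given.

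The Primary endpoint section names one scale, PDI. Secondary endpoints lists three items: a PDI responder target at 2 years, willingness to have the treatment again, and a VAS reduction at 2 years. A separate list then begins "Other outcomes include neuropsychological pain, and cognitive and psychiatric assessments".

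**The concern.** Two steps in the reasoning do not hold. First, a small sample makes it costly to divide alpha, but it does not prevent control of multiplicity. An ordered procedure, or a single designated test, works at any sample size. Second, naming hypotheses in advance guards against choosing results after the fact, but it does not bring the family-wise error of several pre-named tests, each at 0.05, back to 0.05.

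What is at stake is how a mixed result would be read. The article intends to see whether a trend indicates efficacy and to plan later trials from it. PDI power at the plan's own effect size is about 29% with 10 patients. A non-significant PDI result beside one nominally significant secondary scale is therefore a realistic outcome, and the text has no rule that stops the latter being presented as a sign of efficacy.

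**Working it through.** **Inputs from the article.** Effect size 0.5, equal to 7 PDI points, so the implied SD of the paired difference is 7 / 0.5 = 14; "statistical power of 80% on a two-sided test with a type I error probability of 0.05"; 34 patients originally, 10 now; paired t-test at 0.05. **Assumed:** 10 complete pairs, the number of secondary tests, and the correlations between outcomes.

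**1. The plan's own figure.** Power of a paired t-test is the probability that a noncentral t variable (df = n − 1, noncentrality d√n) falls beyond ±t(1 − α/2, n − 1). With d = 0.5 and two-sided α = 0.05, power is 79.5% at n = 33 and 80.8% at n = 34. The stated 34 is reproduced, for a single paired test at undivided alpha.

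**2. What correction costs PDI at n = 10.** At d = 0.5 the noncentrality is 0.5 × √10 = 1.58.

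| Approach | α for PDI | Power, d = 0.5 | Power, d = 1.0 | Effect with 80% power |
|---|---|---|---|---|
| PDI first in a sequence, or alone | 0.05 | 29.3% | 80.3% | 1.00 SD (13.9 points) |
| Bonferroni, 2 tests | 0.025 | 19.2% | 68.2% | 1.14 SD (15.9 points) |
| Bonferroni, 4 tests | 0.0125 | 12.0% | 54.7% | 1.28 SD (18.0 points) |

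The first row is also the power with no correction at all. The article's argument applies to the lower rows only.

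**3. Family-wise error without correction.** For k independent tests at 0.05 it is 1 − 0.95^k:

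- k = 2: 1 − 0.9025 = 9.8%
- k = 4: 1 − 0.8145 = 18.5%

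Simulation of equally correlated paired t-tests at n = 10 (100,000 runs, no true effect on any outcome) gives:

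| Correlation | 2 tests | 4 tests |
|---|---|---|
| 0.3 | 9.5% | 17.4% |
| 0.5 | 9.2% | 16.0% |
| 0.7 | 8.6% | 13.7% |

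In the same simulations a fixed sequence starting with PDI gave 4.8% to 5.1%.

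**4. Which tests form the family.** The analysis sentence compares month 3 of DBS with month 3 of sham. Two of the three listed secondary endpoints are at 2 years, and the Phase VI section says there is no sham stimulation after the third month post-crossover. Those two endpoints cannot enter the comparison as defined. The third is a yes/no answer with no stated time point. The article therefore does not identify which secondary outcomes are tested at month 3, and k = 2 and k = 4 are illustrations rather than counts taken from the plan.

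**The case against.** The case for leaving the text alone has real weight.

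- There is one primary scale, and its type I error is 5% with or without correction. This stands.
- The trial is a phase I pilot limited to 10 patients at the regulator's direction. Its stated goal is safety and feasibility, and efficacy is framed as a possible trend that helps to estimate effect sizes and variances. The lack of correction is disclosed, and the Discussion accepts that the small sample limits inference. This stands, and it keeps the point minor.
- The article says it aims to mitigate type I error, not to control it. Restricting tests to hypotheses stated in advance does limit how many are run and prevents selection afterwards. It would be wrong to say the safeguard does nothing; it does not bring the error across several tests back to 5%.

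A reader might infer something stronger: that about 13 scales are each tested at 0.05, giving 1 − 0.95^13 = 49%, so that a chance finding is likely. The document does not support this. Most of those scales are on the separate list of other outcomes, which the analysis sentence does not say will be tested. Eight of them are Table 1 items, scheduled there at baseline, randomization and months 12 and 24, although the Phase II section says the assessments are repeated in the randomized phase, so their timing is uncertain. The figure also assumes independence and is still below one half.

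What survives the objection is that the reason given for not correcting is wrong, and that unadjusted secondary tests at 0.05 are planned without a descriptive label.

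**Conclusion.** The point holds as a minor one. Small size is not a valid reason to forgo multiplicity control, because giving PDI the first or only test at 0.05 leaves its power where it is: 29.3% at d = 0.5, assuming 10 complete pairs. Stating hypotheses in advance does not replace that control.

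The excess error falls only on secondary claims. Its size depends on a family of tests that the article does not define: about 10% for two independent tests, and 14% to 19% for four, depending on correlation. It would be a misreading to take these figures as the error of the primary analysis.

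**What to change.** In Sample size estimation and efficacy, replace the sentence that correction is not possible and the one on a priori hypotheses with wording to this effect:

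> The month-3 DBS-minus-sham difference in PDI is the only hypothesis test, at two-sided α = 0.05. All other outcomes are exploratory and are reported as estimates with 95% confidence intervals, without claims of significance.

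Amend the following sentence so that it no longer applies the 0.05 test to secondary outcomes.

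A second confirmatory step is not needed. VAS in particular would be a weak candidate: its endpoint is defined only at 2 years, and the Discussion expects that stimulation may change the experience of pain without changing its intensity.

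The cost is a wording change while the trial is still enrolling, with no loss of PDI power. The downside is that no secondary scale can be called significant. Estimates with intervals still serve the stated aim of supplying effect sizes and variances for later trials.

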#### Phase IV: DBS programming and titration

DBS programming is initiated at least a month after DBS surgery to allow for resolution of microlesional effects. In acute programming, patients are asked to report changes in mood, anxiety, pain or suffering with activation of one or more electrode contacts. If the affective reporting of pain is not influenced, then settings affecting mood and anxiety can be chosen for chronic stimulation. All stimulation settings are planned below a charge density of 30 μC/cm^2^/phase, using the formula:

$$\begin{array}{c} \text{Charge}\;\text{density}\;\left({\mathrm{\mu C}/\mathrm{cm}}^{2}/\text{phase}\right)\\ =\frac{\text{Voltage}\;\left(V\right)*\text{Pulse}\;\text{width}\;\left(\mathrm{\mu s}\right)}{\text{Lead}\;\text{surface}\;\text{area}\;\left({\mathrm{cm}}^{2}\right)*\text{Impedance}\;\left(Ω\right)}\;\mathrm{Eq}.\;1 \end{array}$$

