#### Phase V: randomization and intervention

Once optimal settings are determined, stimulation is turned off for about a month in order to minimize the effects of experience and memory of stimulation. Patients are then randomized to either the DBS group that receives active stimulation programmed to the settings found to be optimal during titration in phase IV, or to the sham group that receives 0 V (no electrical current) stimulation. As a technical detail, for minimizing risk to blinding procedures, the pulse generator is always kept on during all phases so that if any patients have tests that could indicate the status of the generator, it will always appear to be turned on Patients are randomized in a 1:1 ratio to one of the two groups.

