## Discussion and conclusions

Our protocol aims to test the safety, feasibility and preliminary efficacy of a novel, neuromodulation therapy for intractable TPS. Our approach is based on the premise that failure of traditional cerebral neuromodulation in TPS with DBS [4,5,13,16] emerges from over-reliance on modifying the percept of pain by stimulating sensory-discriminative substrates that may be unviable owing to the offending lesions. Further, since the affective component of pain experience is equally, if not more important than the perceived intensity of pain, targeting regions such as VS/ALIC may successfully modify pain experience without necessarily modifying perception of pain intensity. The level of evidence, however, supporting efficacy for DBS in chronic neuropathic pain is mainly considered class III (descriptive case series, unblinded designs) [38], attributed to poor control of confounders of therapeutic benefit of neuromodulation. While addressing our research question, we have built study design refinements to potentially inform current and future clinical DBS trials in the field.

The ethical-scientific dilemma of introducing a control arm is particularly intense in neurosurgery, given the risk of interventions to the brain. However, since DBS allows for all patients to be implanted at first and then be randomized to active stimulation or sham, studies have explored randomized controlled designs in the use of DBS, particularly in movement disorders [39-42]. Thus, to balance ethical issues (potentially effective treatment compared against control or less effective treatment) with the importance of generating rigorous empirical evidence, we have incorporated a randomized, controlled, crossover design, where both active DBS and sham groups switch to the other intervention after 3 months from their initial randomization. That therapeutic benefits may carry over from the DBS into the sham phase cannot be completely discounted. By evaluating outcomes between active DBS and sham in the third month of corresponding treatments, we expect to minimize the influence of carry over; by noting difference in outcomes between the third month of the initial treatment and the first month of the intervention after crossover, we may also be able to define an adequate time lapse for future crossover studies.

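### The planned paired t-test leaves out the period factor of the crossover; a period-adjusted analysis would protect the effect estimate and the planning SD for about one power point

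*Protocol article*

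**What the plan says.** All statements are in the Protocol article.

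- **Design.** Under Phase V: "Patients are randomized in a 1:1 ratio to one of the two groups". The Discussion adds that "both active DBS and sham groups switch to the other intervention after 3 months from their initial randomization". This makes two sequences (DBS-first and sham-first) and two periods.
- **Analysis.** For every efficacy endpoint, month-3 values under active stimulation are set against "those in the third month of sham stimulation using the paired *t*-test at α = 0.05" (Sample size estimation and efficacy). Neither period nor sequence is mentioned in the analysis.
- **Sample size.** The same section planned for an "effect size of 0.5 (equivalent to a 7-point decrease in PDI". Its original figure of 34 patients came from requiring "statistical power of 80% on a two-sided test with a type I error probability of 0.05". The regulator then decided that "the study should initially enroll 10 patients as part of a phase I, safety study".
- **Purpose.** That section says the efficacy data are to supply effect sizes and variances for sizing later trials.
- **Carry-over.** The Discussion handles it by using third-month values. Period effects are not discussed.

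**The concern.** In a crossover, each patient's DBS-minus-sham difference contains the treatment effect plus or minus any change between period 1 and period 2. The sign depends on which treatment came first. A paired t-test pools these differences as if they all had the same mean.

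Two things follow if there is a time trend. With equal sequences the trend cancels from the mean but stays in the standard deviation, so the test loses power and the SD passed on to later trials is too large. With unequal sequences the trend no longer cancels from the mean.

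The planning SD is the more important of the two here, since supplying it is one of the stated statistical purposes of a ten-patient trial. The test is named in the article, so this is a stated choice and not a detail left to an unseen analysis plan.

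**Working it through.** **Inputs.** From Sample size estimation and efficacy: effect size 0.5 equal to 7 PDI points, so SD of differences = 7/0.5 = 14; two-sided α 0.05; power 80%; planned N 34; actual N 10. From Phase V: 1:1 allocation, so 5:5 if exactly balanced. The period effect π (period 2 minus period 1) is not in the documents. *Assumption:* 0, 3.5, 7 and 14 points.

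**Step 1: reproduce the plan's N.** For a paired t-test with effect size 0.5, the noncentral t gives power 79.5% at n = 33 and 80.8% at n = 34. The planned 34 is therefore reproduced as a paired-test figure with no period term.

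**Step 2: algebra.** Let D = DBS minus sham, τ the treatment effect, n1 the number DBS-first, n2 the number sham-first, and N = n1 + n2.

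- DBS-first: E[D] = τ − π. Sham-first: E[D] = τ + π.
- Pooled mean: τ + π(n2 − n1)/N.
- Pooled variance: E[s²] = σ² + 4·n1·n2·π²/(N(N − 1)). At 5:5 this is 196 + (100/90)π² = 196 + (10/9)π².

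The period-adjusted estimate is the simple average of the two sequence means of D. In it π cancels whatever the split. Its variance comes from within the sequences, on N − 2 degrees of freedom.

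**Step 3: equal sequences (5:5), true effect 7 points.** The power and type I error of the paired test come from 400,000 simulated trials per case.

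| π | E[s²] | SD of differences | Paired power | Adjusted power | Paired type I error |
|---|---|---|---|---|---|
| 0 | 196.0 | 14.0 | 29.3% | 28.6% | 5.0% |
| 3.5 | 209.6 | 14.5 | 27% | 28.6% | 4.4% |
| 7 | 250.4 | 15.8 | 22% | 28.6% | 3.0% |
| 14 | 413.8 | 20.3 | 8.5% | 28.6% | 0.6% |

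The adjusted test holds its type I error at 5.0% throughout.

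**Step 4: what the inflated SD does to later planning.** Putting each SD into the plan's own calculation (7 points, 80% power, two-sided 0.05, paired t-test) gives N = 34, 36, 43 and 69 for π = 0, 3.5, 7 and 14.

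**Step 5: unequal sequences.** The size of the shift is |n2 − n1|/N times π.

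- 6:4 gives 0.2π: 1.4 points at π = 7 and 2.8 at π = 14.
- 7:3 gives 0.4π: 2.8 and 5.6 points.

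The direction depends on which sequence is larger and on the sign of π. At 7:3 the paired test's type I error is 6.0% (π = 7) and 6.3% (π = 14). The adjusted estimate is unbiased in each case.

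**Step 6: cost of adjusting when π = 0.** At 5:5, power goes from 29.3% to 28.6% (9 to 8 degrees of freedom). At 6:4 it is about 28%, and at 7:3 about 25%.

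**The case against.** **No trend is documented, and the plan guards against one source of it.** This stands. Under Phase IV, "DBS programming is initiated at least a month after DBS surgery to allow for resolution of microlesional effects", and Phase V adds about a month with stimulation off before randomisation. That text describes a safeguard and should not be cited as evidence of a trend. Fading implantation benefit and hope of active treatment could also push in opposite directions. The period effect is therefore an assumed range, and at 3.5 points the power loss is only about 2 points.

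**The planned test is valid on average.** This also stands. At 5:5 it is unbiased and conservative. Over symmetric random allocation the shift averages to zero. The harm is lost precision, an overstated SD, and a shift conditional on the split that actually occurs.

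**Neither analysis is confirmatory at N = 10.** True: power for 7 points is about 29% at best. Assuming a 14-point effect would give more striking power losses, but that is twice the plan's own target.

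**A reader might infer that asymmetric escape makes the bias systematic.** Safety and feasibility describes re-initiation of stimulation or escape for DBS-first patients who relapse, and medical management for sham-first patients. The inference does not support this point. The article does not say that escaped patients leave the analysis, and removal for suicide risk under Endpoints of safety applies to any patient. If they did leave, the loss would be informative and a period term would not repair it. Suppose the two largest responders of five DBS-first patients drop out, with τ = −14 and SD 14. The adjusted estimate is then about −10.1 whether π is 0 or −7, while the paired estimate is −11.1 or −12.8, closer to the truth.

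**A reader might also infer that exact 5:5 balance is not planned.** The article gives only the ratio. How the list is generated is commonly left to the full protocol, so its absence here is no finding.

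**Conclusion.** The point holds as a low-cost improvement to a stated analysis, not as an error that must be corrected before the trial can be interpreted. The named test omits a factor of the design.

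At 5:5 the consequence is an overstated planning SD and lower power, with no bias. It is small for a 3.5-point period effect and substantial from about 7 points. Unequal analysed sequences add a shift of π(n2 − n1)/N.

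These sizes rest on the SD of 14 implied by the plan, a true effect of 7 points, and period effects that are assumed. The stated safety and feasibility goals are unaffected.

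**What to change.** Replace the paired t-test with a period-adjusted crossover analysis. Either compare period differences between the two sequences (Hills-Armitage t-test, 8 degrees of freedom with ten patients), or fit a mixed model with treatment and period as fixed effects and patient as random. Report the within-sequence SD of the differences as the figure for planning later trials.

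The change is to analysis wording only. If there is no period effect it costs one degree of freedom: about 1 power point at 5:5 and about 4 at 7:3. Carry-over and informative departure from the blinded phase are separate problems that this change does not solve.
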